##### The Proportion of Participants Who Perform BSE Regularly and Proficiently

BSE practice and performance frequency will be measured using a self-report answer instrument. Developed by Akhtari-Zavare et al. [12], this instrument incorporates the following questions: (a) Have you ever performed BSE [yes/no], (b) How often do you perform BSE (once a month, once in 2–3 months, other, never). 

A woman who does BSE once a month will be classified as practicing (regular BSE); any other answer will be classified as non-practicing (irregular BSE). The proficiency of performing BSE will be measured by asking the participant to perform BSE on a breast model through BSE proficiency rating instrument (BSEPRI) [29]. This instrument is a checklist assessing the participants’ skills of BSE performance. This assessment is done while the participants demonstrate BSE procedures on a breast model. Needless to say, higher scores indicate greater BSE performance.

##### The Proportion of Participants Who Attend a Clinic for Screening CBE and Mammography

Screening practice regarding CBE and mammography will be assessed using self-report questions assessing participants as “practicing” or “not practicing”.

Using self-reporting in some of the primary outcomes may lead to some sort of bias judgment. Although unavoidable, the researcher tries to reduce this prejudice by being more objective at the data collection stage. This is by using simply precise language, maintaining a short time frame, and assuring confidentiality and anonymity of participants.

#### 2.5.2. Secondary Outcomes

The secondary outcome variables in this study include

##### Knowledge of Breast Cancer

Knowledge of BC and BCS methods will be measured using a modified questionnaire consisting of items adapted from Parsa [30], Akhtari-Zavare et al. [12], McCance et al. [31]. This self-administrated questionnaire consists of 35 items; these include symptoms of BC (6 items), BC risk factors (14 items), breast health awareness (5 items), and BCS methods (10 items). Responses will be evaluated by using the options of the (true, false, I do not know) nominal scale. One score or point will be given for every right answer while zero points for every wrong or uncertain response. The total reliability score for knowledge of BC questionnaire for this study has an acceptable reliability coefficient (α = 0.89). 

##### Beast Cancer Health Beliefs

Health beliefs pertaining to BC will be assessed by the use of a modified version of the CHBMS Champion [32]. The questionnaire consists of 63 self-report measures scales on ten subscales. These are represented as follows: perceived susceptibility to BC (5 items), perceived seriousness of BC (7 items), perceived benefits of BSE (6 items), perceived barriers for BSE (6 items), confidence in one’s ability to do BSE (11 items), health motivation (7 items), benefits of CBE (4 items), barriers of CBE (6 items), benefits of mammography (6 items), and barriers of mammography (5 items). All items will be measured by using the five-point Likert scale via the following list of options: strongly disagree (1 point), disagree (2 points), neutral (3 points), agree (4 points), and strongly agree (5 points). Scores will then be calculated or summated for analysis. With the exception of the barrier item, all other scales are positively related to screening behaviors. The total score reliability for the HBM scale for this study has an acceptable reliability coefficient (α = 0.85).

#### 2.5.3. Other Outcomes

##### Participants’ Personal Information

This part of the questionnaire consists of five questions conducive for assessing the socio-demographic factors of the participants (i.e., age, marital status, education level, income, family history of cancer). In addition, there is another question on previous reading or hearing about BCS.

Lawshe’s method [33] was used to examine the content validity index (CVI) of the questionnaire, indicating a good CVI (CVI = 0.95%). Moreover, the face validity of the questionnaire was initially scrutinized by five professional expert panelists from the Community Health Department and Cancer Resource and Education Centre at the Faculty of Medicine and Health Sciences, Universiti Putra Malaysia. Then some changes on the relevant items were made depending on the suggestions provided by these professional experts. 

### 2.6. Translation of the Questionnaire and Study Module

The questionnaire and study module were translated according to the process of professional translation, while the back translation was used as an approach for the adaptation of instruments [34]. The administration of forward-translation of the original module and questionnaires from English to Arabic language was carried out by an independent PhD health professional from the University of Malaya. The health professional is a native speaker of Arabic and an expert in English and familiar with the terminology of the study topic. With the assistance of the original translator, two bilingual PhD students in English and Arabic languages from Universiti Putra Malaysia were asked to review the translated module and questionnaire. Further, an independent PhD student translator from Universiti Putra Malaysia, whose mother tongue is English and who does not have any knowledge of the module and questionnaire, translated the module and questionnaire back to English. Those translators were instructed to construe the content and confirm the conceptual meanings with an emphasis on the use of acceptable and natural language. Translated versions of the module and questionnaire were compared with the original versions by the study researcher, who then decided the accuracy of the final version of the module and questionnaire. 

Later on, the translated module and questionnaire were pre-tested among 30 Yemeni female school teachers, who are not of the participants in the study. The clarity, understandability, and quality of the module and questionnaire were discussed with them individually. Then, phrases that were unsuitable and/ or difficult to understand were identified, and accordingly, adjustments and modifications thereto were made following their evaluation. Subsequently, the final version was approved for the study.

### 2.7. Sample Size

For the sake of calculating the appropriate sample size for clustering, the standard sample size estimate for the individually randomized design will be calculated. This calculation process is done first by applying the formula to find the difference between two population proportions (power = 0.80, alpha = 0.05 two-sided), (P1 = 0.71, P2 = 0.43 [35]). Then it is inflated by the design effect (design effect = 1.4). The power calculations propose a minimum sample size of 47 participants per arm. This is done by taking into account 20% attrition and 10% expected proportion eligibility. Therefore, a minimum of 183 participants is required for this study.
(1)$$N\;=\;{\left\{1.96\surd 1.14*0.43\;+\;0.84\surd 0.21\;+\;0.25\right\}}^{2}/{\left(0.71\;-\;0.43\right)}^{2}\;=\;47$$

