## 1. Introduction

Although efforts and extensive progress have been made in medical treatment, breast cancer (BC) continues to be among the highest life-threatening diseases among women [1]. It is argued that BC mortality rates in many countries with low and middle income are higher than those in high-income countries. This could be attributed to the early diagnosis of BC in the latter countries. Unfortunately, the diagnosis of BC in the former countries is made at later stages [2]. Yemen, as one of the low-income countries, is a case in point. Most BC cases are identified at late stages or after the occurrence of metastasis [3]. Due to the recent instability of Yemen and lack of security, many Yemenis decided to immigrate to Malaysia for educational purposes and/or job opportunities or to reside as immigrants. As a result, Yemenis in Malaysia have reached a population of about 27,000 according to 2018 estimates of the Yemeni Embassy. Among these are Yemeni females who may not have any idea of BCS services and lack the knowledge and good health beliefs in this regard.

Practically speaking, BC early detection examinations help save thousands of lives each year and improve the chances for early detection of BC, and therefore successful treatment [4]. Several approaches have been evaluated in this respect, such as BCS methods, including BSE, clinical breast exam (CBE), and mammography [5]. A number of epidemiological studies have been conducted on community samples of various women groups. Such studies have shown that the rate of BCS practice was low in various countries [6,7,8]. In Yemen, the findings of similar studies on BSE show that the rate of women performing BSE ranges from 11% to 17.4% [9,10]. 

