### 2.8. Sampling Method

A total number of 12 schools with 183 participants that have met the inclusion and exclusion criteria will take part in the study. Following cluster sampling, six of the schools will be involved in the intervention group, while the other six are the control group. Then the proportionate allocation number of teachers to participate in the study will be calculated based on the density of the teachers in each school (probability proportional to size (PPS). Participants’ selection will be conducted by using a simple random sampling technique.

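### The stated 80% power ignores that only 12 schools are randomised: on a test with 10 degrees of freedom the plan's own inputs give about 73% to 78%

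*Protocol article*

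**What the plan says.** Section 2.7 starts from a comparison of two proportions, "P1 = 0.71, P2 = 0.43 [35", with "power = 0.80, alpha = 0.05 two-sided". Equation (1) uses the normal quantiles 1.96 and 0.84. The article reports the result as follows: "The power calculations propose a minimum sample size of 47 participants per arm". Clustering is handled in one step: "Then it is inflated by the design effect (design effect = 1.4". No intracluster correlation (ICC), mean school size or variation in school size is given behind that value. On losses it says: "This is done by taking into account 20% attrition and 10% expected proportion eligibility". It concludes: "Therefore, a minimum of 183 participants is required for this study".

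Sections 2.8 and 2.11 set the number of clusters at 12 schools, six per arm. Section 2.8 makes the number of teachers taken from each school proportional, "based on the density of the teachers in each school (probability proportional to size (PPS"; it also describes the 183 as people who already meet the eligibility criteria. Section 2.13 names generalized estimating equations (GEE) for the comparison over time.

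**The concern.** A design effect corrects the variance of the arm difference for clustering. It does not correct for the fact that this variance must be estimated from few clusters. With 12 schools in two arms there are 12 − 2 = 10 degrees of freedom between clusters, and a test that keeps its nominal 5% level must use a t critical value of 2.228. The sample-size section combines 80% power with a two-sided alpha of 0.05 as if the 1.96 cut-off were valid.

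The flat value of 1.4 raises a second, smaller question. Sampling in proportion to school size gives unequal clusters wherever schools differ, and unequal clusters increase the design effect for a given ICC.

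At stake is how a null result is read. It would be reported as coming from a trial with 80% power when, at the stated alpha, the design probably has less.

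**Working it through.** **Inputs.** From section 2.7: p1 = 0.71, p2 = 0.43, difference 0.28, design effect 1.4, 20% attrition, and 10% for eligibility (read as a 10% loss, because only that reproduces 183). From sections 2.8 and 2.11: six schools per arm. No ICC or coefficient of variation (CV) of school size is given; values used below are marked as assumed.

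**1. Reproducing the plan.**
- Individually randomised n per arm, with mean proportion 0.57: [1.96·√(2 × 0.57 × 0.43) + 0.84·√(0.71 × 0.29 + 0.43 × 0.57)]² / 0.28² = 47.8. The plan states 47, which is close enough.
- Total: 2 × 47 × 1.4 / 0.8 / 0.9 = 182.8, so 183 is reproduced.
- Normal-test power at an effective 47 per arm is 79% with the pooled variance of equation (1) and 82% with unpooled variance. The stated 80% is therefore right for a normal test.

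**2. The same inputs with 10 df.** Effective n per arm = analysed n / 1.4. SE = √[(0.2059 + 0.2451) / effective n]. Noncentrality = 0.28 / SE. Power is from the noncentral t with 10 df, critical value 2.228.

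| Losses | Analysed per arm | Effective n | SE | Noncentrality | Power |
|---|---|---|---|---|---|
| 20% attrition and 10% eligibility | 183 × 0.8 × 0.9 / 2 ≈ 66 | 47.1 | 0.0978 | 2.86 | 73% |
| 20% attrition only | 183 × 0.8 / 2 = 73.2 | 52.3 | 0.0929 | 3.01 | 77.5% |

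With the pooled variance of equation (1), the first row falls to about 70%.

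**3. Letting the design effect shrink with the schools.** Suppose 1.4 was set at the enrolled size, m = 183 / 12 = 15.25. Then ICC = 0.4 / 14.25 = 0.028.
- Attrition only: m = 12.2, design effect = 1 + 11.2 × 0.028 = 1.31, effective n 55.7, power 80%.
- Both losses: m = 11, design effect 1.28, power 77%.

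Both figures assume equal school sizes.

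**4. Unequal school sizes.** Design effect = 1 + [(1 + CV²)m − 1] × ICC. CV 0.5 is an assumption, and so are the ICCs of 0.036 and 0.05. The calculation applies only if 1.4 does not already allow for size variation. At 66 per arm, m = 11:
- ICC 0.036: design effect 1 + (13.75 − 1) × 0.036 = 1.46, power 71.5% (74.5% with equal sizes).
- ICC 0.05: design effect 1 + 12.75 × 0.05 = 1.64, power 66.6% (70.3% with equal sizes).

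Inequality of this degree therefore costs about 3 to 4 points. The rest of the fall at ICC 0.05 comes from an ICC that gives a design effect of 1.5 even with equal schools, which is above the plan's 1.4.

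**5. Keeping 1.96.** If the test statistic behaves like t with 10 df, P(|t| > 1.96) = 7.8%. The missing power can be recovered this way only by giving up the stated 5% level.

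**6. Detectable difference.** With control proportion 0.43, design effect 1.4 and 10 df, 80% power needs a difference of about 30 points at 66 per arm and about 29 points at 73 per arm, against the 28 assumed.

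**The case against.** The best defence is that 73% is the low end of the plan's own inputs. Section 2.8 says the 183 already meet the criteria, and section 2.12 places consent and baseline data before the envelopes are opened. The eligibility margin may therefore never be lost. If the design effect also falls as schools shrink, the plan just reaches 80%. This stands, and it is why a range is reported. A reader might infer that power is simply 73%; the documents do not support one figure. The 80% case, however, needs equal schools, which proportional allocation makes unlikely.

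The size of the loss from unequal schools cannot be taken from the article. It gives no school sizes, and 1.4 may already include some allowance. This also stands: the direction is sound, but the amount is illustrative.

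The analysis plan might specify a small-sample correction for GEE, and adjustment for baseline or repeated measures might recover some power. Neither enters section 2.7. A correction would remove the inflated alpha but leave power near the 10-df values. With no losses at all (183 analysed, design effect 1.4), power would be about 86%, but the plan itself expects 20% attrition.

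A reader might also infer a much larger shortfall from the introduction, which says of Yemen that "the rate of women performing BSE ranges from 11% to 17.4" percent, well below the assumed 0.43. The documents do not support that. Those rates come from studies in Yemen, while the trial enrols teachers in Malaysia. The effect on power also depends on what is held constant: at 66 per arm with 10 df, power is 51% to 64% if the odds ratio (0.71/0.29)/(0.43/0.57) = 3.25 is kept, but 85% to 79% if the 28-point difference is kept. The plan assumes no constant odds ratio, so this argument forms no part of the point.

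**Conclusion.** The point holds with moderate size. The arithmetic to 183 is sound, but power of 0.80 and two-sided alpha of 0.05 do not hold together for six schools per arm under the plan's flat design effect. At 1.4, a valid 10-df test has about 73% power with both losses and about 78% with attrition only, a shortfall of roughly 2 to 7 points. The figure of 80% is met only under the joint conditions of no eligibility loss, equal schools and a design effect of about 1.31.

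Unequal schools would lower power by a few points more; about 67% to 72% at 66 per arm is an illustration under an assumed CV of 0.5 and ICC of 0.036 to 0.05. The results rest on the plan's 0.71 versus 0.43, unpooled variance and a between-school test without covariate gains. They do not show that the trial is badly underpowered or that more schools are required.

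**What to change.** Keep 183 teachers and 12 schools. In section 2.7, replace the statement of 0.80 power by the power under a test with 10 df, given as a range: about 73% to 78% at design effect 1.4. Next to it, state the attrition assumed, whether the 10% eligibility margin applies to the 183, the ICC and school size behind 1.4, and the actual CV of the 12 school sizes, recomputing the range with that CV. Alternatively, give the detectable difference at 80% power, about 29 to 30 points before unequal sizes.

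The cost is a short recalculation and a changed sentence. The trial team can obtain the school sizes, since proportional allocation requires them. No extra schools, teachers or procedures are needed.

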### 2.8. Sampling Method

A total number of 12 schools with 183 participants that have met the inclusion and exclusion criteria will take part in the study. Following cluster sampling, six of the schools will be involved in the intervention group, while the other six are the control group. Then the proportionate allocation number of teachers to participate in the study will be calculated based on the density of the teachers in each school (probability proportional to size (PPS). Participants’ selection will be conducted by using a simple random sampling technique.

### 2.9. Participant Recruitment 

Nineteen Arabic schools with 289 Yemeni teachers were assessed for eligibility. Seven schools with 39 teachers were not eligible to take part in the study. In other words, whereas three schools did not show any will and interest to take part in the study, the remaining four schools did not meet the inclusion criteria as they did not include any Yemeni teachers.

With respect to the 12 eligible schools (12 schools), they will be invited to contribute to the study. Written consent will be obtained from respective authorities in all the schools. With the help of school coordinators, eligible teachers would be invited to attend small meeting groups in each school. During such meetings, the researcher will explain the objectives and advantages of the study, along with the inclusion and exclusion criteria. After selecting the required participants’ number in each school, participants will be asked for written informed consent. Accordingly, participants who agree to participate will be asked to fill in the questionnaire. Later on, educational interventions on BCS will be delivered to the intervention group. Following that, the participants will be requested to fill in the same set of the questionnaires (with the exception of the personal information form) in the post and follow-up assessment. 

### 2.10. Study Principles

The reporting of this protocol followed the Standard Protocol Items: Recommendations for Interventional Trials (SPIRIT) 2013 Statement [36]. The study reporting will be in accordance with the Consolidated Standards of Reporting Trials (CONSORT) statement.

Figure 1 below illustrates the Consolidated Standards of Reporting Trials (CONSORT) flowchart [37].

### 2.11. Randomization

The unit of randomization in this current study is a school. To allocate the twelve eligible clusters (schools) to the study groups, an independent statistician will create the randomization sequence using the Sealed Envelope tool [38], with a 1:1 allocation using random block sizes of 2 and 4. Thus, six clusters were randomly allocated to the intervention group (VX9, XP6, EP9, ZI8, FF5, and IQ3) and six clusters to the control group (IO2, OM1, BM3, AT1, AA4, and KM3).

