## 2. Materials and Methods

### 2.1. Study Design

This is a parallel cluster-randomized controlled trial (cRCT), with schools being the unit of randomization (clusters). The trial will be used to assess the effectiveness of an educational intervention on BCS uptake, knowledge, and beliefs of Yemeni female school teachers at both elementary and high Arabic schools in Klang Valley, Malaysia. There are nineteen well-known Arabic schools in Klang Valley area, with teachers from different Arab countries (i.e., Yemen, Iraq, Egypt, Libya, Saudi Arabia). However, the main composition of the teaching bodies is Yemeni teachers, as six of the schools are Yemeni schools. Twelve of the schools were selected as clusters (schools), and randomly assigned for the intervention or the control group. While the intervention group was given an educational intervention on BCS, the control group received the educational materials on BCS intervention after the completion of the study. 

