### 2.2. Eligibility Criteria

The inclusion criteria for schools will take into account the following requirements: (1) such samples are elementary and high Arabic schools; (2) they are situated in Klang Valley; (3); and they consent to participate in the study. The exclusion criteria will disqualify Arabic schools that do not have Yemeni female teachers from the study,

The inclusion criteria for teachers takes into consideration the following requirements: (1) such participants must only be Yemeni female school teachers teaching at the selected elementary and high Arabic schools situated in Klang Valley; (2) participants are aged 20 years old or older; (3) they sign a consent form to take part in the study. The exclusion criteria for teachers include (1) teachers who are retiring during the study, (2) teachers who have been diagnosed with BC, and (3) teachers who are lactating or pregnant.

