### 2.12. Allocation Concealment Mechanism

To ensure proper allocation concealment, a statistician will be assigned to produce the allocation sequence list by using block randomization software. Each cluster will be given a unique code in a sealed opaque envelope. Following that, the research assistant will open the envelopes and assign the clusters to the intervention or control group based on the list of codes generated by the software. Moreover, to avoid bias at the individual level, the envelopes will be opened only after the school coordinator selects the required participant number, and after obtaining consent for treatment and collecting baseline data.

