### 2.13. Statistical Analyses

IBM SPSS Software 25.0 (SPSS Inc. Chicago, IL, USA) will be used to analyze collected data. However, missing data will be managed by adopting the intention-to-treat analysis concept. Prior to analysis, continuous variables will be checked for normality. The alpha level of significance will be set at the value of <0.05. Descriptive analysis will be employed to describe the data at baseline. Regarding the between-group comparisons, the chi-square test will be applied to compare the frequency difference of categorical data of the intervention with that of the control groups. The independent-samples *t*-test will be applied to compare the mean difference of continuous data of the intervention with that of the control group. 

Furthermore, to evaluate the changes within both groups, Cochran’s Q test will be applied to test the frequency differences of categorical data within the study groups’ overtimes. The one-way repeated measures ANOVA will be applied to identify the mean difference within the study groups for continuous variables overtimes. Generalized estimating equations will be used to test the main effect and interaction between and within the overtimes of the intervention and control groups.

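### Blocks of 2 and 4 over 12 known schools balance only the number of schools per arm; the between-arm conclusion should rest on a cluster-aware model adjusted for age and baseline outcome, not on unadjusted tests

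*Protocol article*

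**What the plan says.** - **Allocation.** Section 2.1 makes the school the unit: "Twelve of the schools were selected as clusters (schools), and randomly assigned for the intervention or the control group". Section 2.11 has an independent statistician generate the list "with a 1:1 allocation using random block sizes of 2 and 4". It names no stratification, matching or constraint. It also lists six school codes under each arm as already allocated, while using the future tense for the sequence.
- **Timing.** Under section 2.9 the 12 schools are identified before anything else happens. Under section 2.12 "the envelopes will be opened only after the school coordinator selects the required participant number, and after obtaining consent for treatment and collecting baseline data".
- **Differences between schools and women.** Section 2.1 says of the nineteen Arabic schools in the area: "However, the main composition of the teaching bodies is Yemeni teachers, as six of the schools are Yemeni schools". Section 2.2 admits both elementary and high schools, and women from age 20 with no upper limit.
- **Baseline data.** Section 2.5.3 records age, marital status, education, income and family history. Section 2.3 has both arms answer the same questionnaires at baseline and at each follow-up.
- **Analysis.** Section 2.13 uses baseline data descriptively. It compares the arms by chi-square and independent-samples t-test, then adds a model: "Generalized estimating equations will be used to test the main effect and interaction between and within the overtimes of the intervention and control groups". No covariate is named.

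**The concern.** Permuted blocks keep arm sizes close while participants accrue over time. Here the list is fixed at 12 schools whose features are known before allocation, so blocking delivers little beyond an even count of schools. Each school is one sixth of its arm, so one or two schools of a given kind falling on one side changes the arm's make-up visibly.

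Chi-square and t-tests take no account of such a difference, nor does a group main effect from a model holding only group and time. If the arms turn out uneven in age or school type, a positive result on these comparisons can be challenged. Any adjustment chosen after the imbalance is seen will look selective. The variables needed to prevent this are already being collected.

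**Working it through.** **1. The plan's own sample size.** The printed equation in section 2.7 (0.71 against 0.43, two-sided 0.05, 80% power) evaluates to 48.1 per arm; the article states 47. From 47: 47 × 1.4 × 2 = 131.6; 131.6 / 0.80 = 164.5; 164.5 / 0.90 = 182.8, so 183. The total reproduces, and the point does not depend on it.

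**2. How many of the 12 are Yemeni schools.** Section 2.1 gives six among nineteen. Section 2.9 removes seven: four without any Yemeni teachers, taken here not to be Yemeni schools, and three that declined. At most three of the six are lost, so between 3 and 6 remain. The article does not give the number.

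**3. Chance of an uneven split.** With K Yemeni schools among 12 and six schools per arm, P(x in one arm) = C(K,x) × C(12−K,6−x) / C(12,6), and C(12,6) = 924.

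| K | Uneven split | Probability |
|---|---|---|
| 6 | 4:2 or worse | 57% |
| 6 | 5:1 or worse | 8% |
| 5 | 4:1 or worse | 24% |
| 4 | 3:1 or worse | 55% |
| 4 | 4:0 | 6% |
| 3 | 3:0 | 18% |

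Simulating 60,000 lists with random blocks of 2 and 4, schools in random order and 6:6 lists kept, gives 56% and 8% for K = 6. Blocking does not reduce the imbalance. A draw within type gives 3:3 and still leaves 20 × 20 = 400 of the 924 allocations.

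**4. Age.** With 183/12 = 15.25 women per school and an assumed intraclass correlation (ICC) of age of 0.03 to 0.20, the SD of the difference in arm means is √[2 × (ICC + (1 − ICC)/15.25)/6] = 0.177 to 0.290 individual SDs. The probability that arm means differ by more than 0.2 SD is 0.26 to 0.49.

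**5. Shift in an unadjusted post-baseline comparison.** Shift = type difference × (difference in counts)/6, taking schools as equal in size. With an assumed type difference of 10, 20 or 30 points, a 4:2 split moves the arm difference by 3.3, 6.7 or 10 points. A 5:1 split moves it by 6.7, 13.3 or 20. The planned effect is 71 − 43 = 28 points.

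**6. Power from adjusting for school type (K = 6, balanced).**
- Analysed: 183 × 0.80 = 146 women, or 12.17 per school.
- Implied ICC: 0.4/11.17 = 0.036.
- Mean binomial variance: (0.71 × 0.29 + 0.43 × 0.57)/2 = 0.2255.
- Between-school variance: 0.036 × 0.2255 = 0.0081, SD 9.0 points.
- Variance of a school mean: 0.2255 × 1.4/12.17 = 0.0259.
- Standard error of the arm difference: √(2 × 0.0259/6) = 0.093.
- Noncentrality: 0.28/0.093 = 3.01. With 10 degrees of freedom, power is 77%.

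Adjusting removes (type difference/2)² from the variance of a school mean and leaves 9 degrees of freedom:

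| Assumed type difference | Noncentrality | Power |
|---|---|---|
| 0 points | 3.01 | 76% |
| 5 points | 3.05 | 77% |
| 10 points | 3.17 | 80% |
| 15 points | 3.40 | 86% |

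At 15 points, school type would have to explain 0.0056/0.0081, about 70%, of all between-school variance.

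**The case against.** **Does the imbalance go uncorrected throughout?** A reader might infer so. The article does not support that. Baseline is one of the assessments, and the abstract gives the purpose of the GEE as differential change over time. A level difference between school types or ages that stays constant largely cancels in the group-by-time contrast, so the shifts in step 5 do not apply to it. They apply to the chi-square and t-test comparisons and the group main effect. Effects of age or school type on change also remain, which is plausible for mammography uptake.

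**Was adjustment ruled out?** A condensed article may leave covariates to an analysis plan that is not shown, and nothing excludes them. This stands, so silence on covariates is not the point. The unadjusted tests are stated, and the point rests on those. They could be meant for baseline tables only, but section 2.13 sets no such limit.

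**Is it bias?** No. Unstratified randomisation of clusters is valid, and a correct cluster-level standard error includes chance imbalance.

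**Does school type matter?** Unknown. All participants are Yemeni women teachers, and no section says practice differs by type. This stands and is why type is optional in the fix.

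**Could later assignments be guessed from small blocks?** A reader might infer this too. Section 2.12 does not say envelopes are opened one school at a time. Women are selected, consented and assessed at baseline before opening, which limits any harm.

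**Conclusion.** The concern holds in a limited form. With 12 schools known in advance, the stated scheme controls only the count per arm. A 4:2 or worse split has probability 57% if six are Yemeni schools, and arm mean ages differ by more than 0.2 SD with probability 0.26 to 0.49. The first figure rests on an assumed number of Yemeni schools, the second on an assumed ICC of age.

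The exposed analyses are the chi-square and t-test comparisons, the GEE group main effect, and any effect of age or school type on change. The consequence is lost precision and a result that is easier to dispute. The power gain from school type is modest and conditional: three points at a 10-point type difference, none at 5, minus one at zero. The case for change rests mainly on adjusting for age and baseline outcome, which does not need school type to matter.

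**What to change.** **Section 2.13.** Base the between-arm conclusion on a post-baseline model that accounts for school as the cluster and adjusts for the woman's age and the baseline value of the outcome, in place of the unadjusted chi-square and t-tests. State this before outcome data are examined. Age comes from the personal information form and baseline answers from the first questionnaire, so there is no new data collection and no change to the 183. The cost is wording.

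**School type.** It may be added as one fixed covariate, using one of the 12 − 2 = 10 school-level degrees of freedom. With so few schools the covariate list should stay short.

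**Section 2.11.** State plainly whether allocation has been made. The listed codes suggest it has, in which case a redraw is too late. Only if it has not, replace the blocks by a single draw within school type, as evenly as the counts allow (an exact half is impossible with 3 or 5 Yemeni schools), and unseal all 12 together after the last baseline. That makes the first schools wait for the last.
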